#### Blinding {17a}

Once the completed baseline questionnaire (t0) is returned to the data evaluation institution, the research team will identify study IDs that are assigned to the IG and prepare the sending of the DA in a closed envelope. This envelope will be solely marked with the study ID. An independent entity neither belonging to the research team nor the recruiting team will decode the study ID, prepare the envelope with the name and address of the participants and send it off. The supervising study nurse remains blinded to the allocation to the study group throughout the study. This also applies to the recruiting physicians. However, it cannot be ruled out that treating physicians could be unblinded if participants approach them about the study at a follow-up appointment. At t0, all trial participants are blinded. The data analysts will be blinded with regard to group allocation by coding group allocation before data analysis.

#### Unblinding {17b}

Due to the nature of this study, unblinding for the participants will occur as soon as they receive the DAs. The same applies to participants who receive the follow-up questionnaires at t1 and have not received a DA by then. With the exception of the statistician who is responsible for data analysis, the research team will be able to assign the evaluated data to the two study groups and therefore will not be blinded.

### Data collection, management and analysis

#### Data collection methods {18a}

The completed questionnaires are sent to the data evaluation institution, where the research team collects the data and transfers them into a digital form on a password-protected computer. The research team is neither involved in post-test genetic counselling nor in recruitment of the participants.

#### Promoting participant retention and complete follow-up {18b}

Participants who did not return the questionnaires in time will receive up to two postal reminders with the request to send the questionnaires back within 1 week. Those who still will not react will be contacted again by telephone to encourage participant retention. This will be done by the study nurse who works with the recruiting team.

Women assigned to the CG do not receive DAs and may, therefore, be more likely to drop out of the study than women assigned to the IG. To counter this possibility of higher drop-out rates, all women in the CG are offered to request a DA when the last follow-up questionnaire at t2 is returned. This is to ensure that they can participate in the study without being disadvantaged.

#### Data management {19}

The paper-based data from the returned pseudonymised questionnaires will be transferred into digital data using the software programme Remark Office OMR. For quality control and verification, all the extracted data is also manually checked by members of the research team. According to the German data protection guidelines, the paper-based questionnaires are kept in a securely locked location, as are the digital data which is stored on a notebook with password protection and kept in a securely locked location. Solely, the members of the research team have access to these data.

#### Confidentiality {27}

According to the German data protection guidelines, personal information about potential and enrolled participants is kept strictly separate from the study data in order to maintain confidentiality before, during and after the trial. Personal data is only known to the recruiting physicians, the study nurse and one independent person who is responsible for sending the DAs to the IG participants (see the ‘Blinding {17a}’ section). Only these persons will have a list that allows the study IDs to be matched to the personal data of the participants. This assignment list will be kept strictly separate from the study data collected by the research team. The research team will never have access to the participants’ personal data but will only receive pseudonymised questionnaires.

#### Biological specimens {33}

No biological specimen will be collected.

## Statistical methods

### Analysing primary and secondary outcomes {20a}

Analysis of the baseline data (t0) will be done to ensure the comparability of the two study groups. Outcomes are measured at t1 and t2. All primary and secondary effectiveness variables will be described by statistical characteristics values. Continuous data will be described by mean, standard deviation, median, minimum and maximum. Categorical data will be described by using frequencies and percentages. The number of non-missing values will also be given.

The primary outcome at t1 is decisional conflict. The mean differences of the primary outcome between both groups will be compared using the independent *t-*test in case of normal distribution. In addition, the mean differences in the score within the groups between t0 and t1 will be compared using a dependent *t-*test. Non-parametric tests will be used in case of non-normal distribution. Secondary outcomes comprise the mean differences in scores of the stage of decision-making, stress, anxiety and depressive symptoms between t0, t1 and t2. A further secondary outcome measured at t2 is the regret of the decision. For these analyses, a dependent respectively independent *t-*test will be used in case of normal distribution, non-parametric tests will be used in case of non-normal distribution. Data will be analysed by using IBM SPSS Statistics for Windows, version 27.0 (IBM Corp: Armonk, NY) and R [71]. An alpha level of 0.05 is considered significant in all statistical tests.

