**Methods:**

A sample of 310 women carrying *BRCA1/2* mutations (A) without a history of cancer or (B) with a history of unilateral breast cancer who have received post-test genetic counselling will be enrolled. Upon study consent, women will be randomly assigned to either the intervention or the control group. All participants will receive standard care including a physician’s letter summarising the counselling content. After baseline data collection (t0), the intervention group receives the respective decision aid while the control group receives standard care only. The primary outcome variable assessed at a 3-month follow-up (t1) is the change of extent in decisional conflict (measured with the Decisional Conflict Scale). Secondary outcome variables comprise the stage of decision-making, self-reported symptoms of anxiety, depression and stress due to the genetic test result, and knowledge regarding cancer risks and preventive options. At t1, the extent of preparation for decision-making and acceptability of the decision aids will also be examined. Another secondary outcome variable assessed at 6-month follow-up (t2) is the extent of decision regret.

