**Table 1 Tab1:**
[figure not shown]
Outcome parameters and time points for outcome measurements

The primary outcome at 3-month follow-up (t1) is the change in the extent of decisional conflict measured with the DCS. Secondary outcome variables at t1 include changes in SDM-S, HADS, IES-R and knowledge. Additionally, at t1, the items addressing the preparation for decision-making as measured with the Preparation for Decision Making Scale (PrepDMS) [56, 57] and the acceptability of the DAs compared to control by the participants as measured with an acceptability instrument [30, 58] are collected. Secondary outcome variables at t2 comprise SDM-S, DCS, HADS and the extent of regret for the decision made as measured with the Decision Regret Scale (DRS) [59]. It is possible that no final decision has been made at t2 or that the decisions made at t2 are only temporary.

The evaluation instruments are described below.

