#### Decisional conflict

Decisional conflict is measured using the Decisional Conflict Scale (DCS) [51, 60]. It comprises five subscales with a total of 16 items, which are assessed on a 5-point Likert scale (from 1 = strongly agree to 5 = strongly disagree). The subscales concern the following topics: being informed, clarification of personal values, support or pressure from others, uncertainty about the decision and the assessment of one’s own decision-making. The German version of the DCS has been shown to have good psychometric properties, with a reported internal consistency of Cronbach’s alpha = 0.78 or higher [60]. The DCS is administered at t0, t1 and t2.

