#### Allocation: sequence generation {16a}

Study participants will be randomly assigned to either IG or CG with a 1:1 allocation. Sequence generation is done with a computerised random number generator by a member of the research team who is not involved in data analysis.

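### The primary outcome reads as a change in one section and a level in another, and the unadjusted t-test fixed for it forgoes the precision that baseline DCS would give

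*Protocol article*

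**What the plan says.** Outcomes {12} defines the endpoint as a change: "The primary outcome at 3-month follow-up (t1) is the change in the extent of decisional conflict measured with the DCS". The abstract agrees; the primary outcome there "is the change of extent in decisional conflict (measured with the Decisional Conflict Scale"). The analysis section {20a} drops the word change: "The primary outcome at t1 is decisional conflict". It then fixes the between-group test: "The mean differences of the primary outcome between both groups will be compared using the independent" *t*-test, in case of normal distribution. As an addition, "the mean differences in the score within the groups between t0 and t1 will be compared using a dependent" *t*-test. The alternative is left general: "Non-parametric tests will be used in case of non-normal distribution". No test or criterion for normality is given, the replacement test is not named, and no covariate is mentioned.

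The baseline score is available: "The DCS is administered at t0, t1 and t2". In {20a} the t0 data serve a comparability check and the paired within-group tests. Sample size {14} uses Cohen's d = 0.3 with a one-sided *t*-test and does not say whether d is in SDs of the t1 score or of the change.

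**The concern.** Two primary endpoints (level, change) and two kinds of test (*t*-test, rank test) are all compatible with the text, so four primary analyses are open when the data arrive. They do not give the same answer. The level and change estimates differ by exactly the baseline difference between the arms, and a rank test does not estimate a mean difference at all.

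Neither *t*-test makes the best use of baseline DCS. The level test leaves it out; the change test subtracts it in full, whatever its correlation with the follow-up score. The plan examines baseline comparability in {20a}, and again in the interim look at t0 data in {21b}, but the primary comparison has no means of correcting an imbalance if one is found. At stake are precision and a primary result that cannot depend on choices made after the data are seen.

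**Working it through.** **The plan's own figure.** Inputs from Sample size {14}: d = 0.3, one-sided α = 0.05, power 0.80 (printed as ß of 0.8, which reproduces only as power), drop-out 10%. The exact noncentral-*t* solution is 138.07 per group, rounded up to 139. Then 139/0.9 = 154.4, so 155 per group and 310 in total. All three figures reproduce. Power at 139 per group is 80.2%.

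**Assumptions for the comparison.** The t0–t1 correlation r of the DCS is not in the document, so r = 0.3, 0.5 and 0.7 are assumed. SDs at t0 and t1 are taken as equal. All power figures are noncentral-*t*, 139 per arm, one-sided 0.05.

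**If d = 0.3 is in SDs of the t1 score.** Relative to the t1 variance, the variance is 1 for the level, 2(1 − r) for the change and 1 − r² for ANCOVA. The effective d is 0.3 divided by the square root of each.

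| r | Change: d, power | Level: d, power | ANCOVA: d, power |
|---|---|---|---|
| 0.3 | 0.3/√1.4 = 0.254, 67.9% | 0.3, 80.2% | 0.3/√0.91 = 0.314, 83.4% |
| 0.5 | 0.3/√1.0 = 0.300, 80.2% | 0.3, 80.2% | 0.3/√0.75 = 0.346, 89.2% |
| 0.7 | 0.3/√0.6 = 0.387, 94.2% | 0.3, 80.2% | 0.3/√0.51 = 0.420, 96.8% |

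**If d = 0.3 is in SDs of the change score.** The change *t*-test has 80.2% at every r. The ANCOVA variance relative to the change variance is (1 − r²)/(2(1 − r)) = (1 + r)/2.

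| r | ANCOVA: d | Power |
|---|---|---|
| 0.3 | 0.3/√0.65 = 0.372 | 92.6% |
| 0.5 | 0.3/√0.75 = 0.346 | 89.2% |
| 0.7 | 0.3/√0.85 = 0.325 | 85.6% |

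**Does the ordering depend on equal SDs?** Let k = SD(t0)/SD(t1). The change variance is 1 + k² − 2rk. Subtracting 1 − r² leaves (k − r)², which is never negative. ANCOVA is therefore at least as precise as the change test for any k, and at least as precise as the level test because 1 − r² ≤ 1. Only the size of the gain over the change test depends on k.

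**Chance imbalance.** The standard error of the baseline difference, in SD units, is √(2/139) = 0.12. A difference beyond 0.2 SD in either direction has probability of about 10%. Given a baseline difference δ, the level comparison is shifted by rδ and the change comparison by −(1 − r)δ. With r = 0.5 and δ = 0.2 these are +0.10 and −0.10 SD, each a third of the planned 0.3. ANCOVA removes the shift.

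**Normality gate.** Simulation: 6,000 trials per setting, r = 0.5, t1 level, with Shapiro–Wilk at 5% in each arm and then Mann–Whitney (an assumed rule, since none is stated). Type I error was 0.050 with normal data and 0.048 with skewed data. Power was 0.80 with normal data. About 10% of truly normal data sets, and all of the skewed ones, were sent to the rank test.

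**The case against.** - **Section {20a} may be shorthand.** Both explicit definitions are a change, and the analysis section can be read as that same change score. Baseline then enters by subtraction, and {20a} also uses t0 in paired tests. This stands: a reader might infer that the plan ignores baseline DCS, but that is true only on the level reading. On the change reading the fault is inefficient use.
- **The trial is not undersized on its own inputs.** This stands. A reader might take the 68% figure as a power deficit. It arises only if d is on the t1 scale, r is 0.3, the SDs are equal and the change is tested. With d on the change scale it disappears. If SD(t0) were 0.8 of SD(t1) (illustrative), the change variance at r = 0.3 is 1 + 0.64 − 0.48 = 1.16, effective d is 0.3/√1.16 = 0.279, and power is about 75%.
- **Randomisation already supplies balance.** Also right: either *t*-test is unbiased over randomisation. Only correction of the imbalance that happens to occur is forgone.
- **The gate is nearly harmless to error rates.** The simulation agrees. With the skewed data, power was even higher through the gate (0.893) than with the *t*-test on the level (0.812), and close to ANCOVA (0.888). The remaining objection is that the data decide which effect measure is reported.
- **Cancer history and recruitment route are covered by the subgroup analyses in {20b}, and a condensed article need not describe stratification.** Accepted. No gain has been quantified for either covariate, so neither is pressed.
- **A separate analysis plan may settle the model.** It may, but this article names the test and gives both versions of the endpoint. A plan consistent with it would inherit both problems.

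**Conclusion.** The point holds as one of efficiency and an unfixed primary estimate, and should be corrected. It is not an error of sample size, a source of bias or an invalid test, and the document does not support any of those stronger readings.

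At the planned 139 per arm, baseline adjustment raises power from 80% (level test) to 83, 89 or 97% for correlations of 0.3, 0.5 or 0.7 when d is in t1 SDs. When d is in change SDs it raises power from 80% (change test) to 93, 89 or 86%. Leaving level or change open moves power, for the same raw effect on the t1 scale, by about −12 points (80.2 to 67.9) at r = 0.3 and +14 points (80.2 to 94.2) at r = 0.7. The direction of the gain is certain under either reading; its size rests on the assumed correlation and, for the change-score comparisons, on equal SDs at t0 and t1.

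**What to change.** In {20a}, make the primary analysis a linear regression of DCS at t1 on arm and DCS at t0. Report the adjusted mean difference with its confidence interval, and use this model whatever a normality check shows. Keep a named rank test as a sensitivity analysis only. Cancer history and recruitment route may be added as optional covariates. Use the same description of the endpoint in the abstract, {12} and {20a}. Once baseline is a covariate the arm effect is identical whether the response is the level or the change, so this settles the ambiguity without discarding either definition.

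No new data are needed. The t1 questionnaire goes only to women who returned t0, so adjustment should lose almost no one beyond incomplete baseline items. The cost is procedural. Recruitment closed on 30 September 2021, the research team other than the statistician is not blinded ({17b}), and amendments need ethics approval before use ({25}). The change should therefore be a dated amendment, made before outcome data are analysed by arm.

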#### Subjective stress symptoms because of the genetic test result

To determine the impact of the genetic test result of having a pathogenic *BRCA1/2* mutation on subjective stress symptoms the German version of the Impact of Event Scale-Revised (IES-R) is used [63]. The IES-R contains a total of 22 items in three subscales referred to as intrusion, avoidance and hyperarousal. They are assessed using a 4-point Likert scale (from 0 = not at all to 5 = often). The values of the three subscales can be used to calculate the probability of diagnosing a post-traumatic stress disorder. The IES-R is administered at t0 and t1.

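### Within-arm paired tests at 0.05 are added to the trial's comparisons, and the wording for the repeated secondary outcomes does not secure a between-arm test

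*Protocol article*

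**What the plan says.** All of the analysis text is in the protocol article, section Analysing primary and secondary outcomes {20a}.

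- **Primary outcome, between arms:** "The mean differences of the primary outcome between both groups will be compared using the independent" t-test, if the data are normally distributed.
- **Primary outcome, within arms:** "In addition, the mean differences in the score within the groups between t0 and t1 will be compared using a dependent" t-test.
- **Repeated secondary outcomes:** these are defined as the "mean differences in scores of the stage of decision-making, stress, anxiety and depressive symptoms between t0, t1 and t2". Decision regret at t2 follows as a further secondary outcome. The test for the whole group is then given: "For these analyses, a dependent respectively independent" t-test, or a non-parametric test.
- **Significance level:** "An alpha level of 0.05 is considered significant in all statistical tests".

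Two other sections bear on this. Objectives {7} frames the primary hypothesis as the aid on top of standard care against standard care alone, and asks whether the aids reduce anxiety, depression and strain. The measurement schedule says of the stress instrument: "The IES-R is administered at t0 and t1". The list under Outcomes {12} agrees: "Secondary outcome variables at t2 comprise SDM-S, DCS, HADS and the extent of regret for the decision made". That t2 list does not contain the IES-R.

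**The concern.** A paired test inside one arm asks whether scores moved since baseline. Decisional conflict and distress may fall after a genetic diagnosis and counselling whether or not a woman receives a decision aid, and such a test cannot separate that fall from an effect of the aid. It makes no use of the randomised comparison.

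Nothing in the section marks the within-arm tests as descriptive. Description has its own sentences (mean, standard deviation, median, range), and the 0.05 level covers every test.

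The secondary outcomes are less well fixed than the primary. They are defined as changes over time, and the test is named by a phrase that can be taken in order: the paired test for the change outcomes, and the independent test for regret, which has no baseline. Read that way, anxiety, depression and strain would have no treatment comparison, although the objectives ask about them.

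The risk is that a significant fall in the intervention arm beside a non-significant one in the control arm is taken as benefit.

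**Working it through.** **1. The plan's own figure.** Sample size {14} gives d = 0.3, one-sided alpha 0.05, power 0.8 and 139 per group.

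- Normal approximation: n = 2(1.645 + 0.842)² / 0.3² = 137.4, so 138.
- Exact noncentral t: 138.07, so 139. This reproduces the stated figure; power at 139 per group is 80.2%.
- Dropout of 10%: 139 / 0.9 = 154.4, so 155 per group and 310 in total, as stated.

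The sample size therefore rests on the between-arm test alone.

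**2. How often within-arm tests mislead.** Inputs:

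- n = 139 per arm, from the protocol.
- Alpha 0.05, from the protocol. Two-sided is assumed here, because {20a} does not state the sidedness.
- No effect of the aid, and the same standardised paired change dz (mean change divided by the standard deviation of change) in both arms. The dz values are assumptions: the protocol gives neither a standard deviation nor a within-person correlation.

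For one arm, the probability of significance is p = P(|T| > 1.977), where T is noncentral t with 138 degrees of freedom and noncentrality dz × √139. The arms are independent, so intervention arm only is p(1 − p) and both arms is p².

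| dz | noncentrality | p per arm | intervention arm only | both arms |
|---|---|---|---|---|
| 0.10 | 1.18 | 21.6% | 17% | 5% |
| 0.166 | 1.96 | 49.3% | 25% | 24% |
| 0.25 | 2.95 | 83.3% | 14% | 69% |
| 0.40 | 4.72 | 99.7% | 0.3% | 99% |

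The value 0.166 lies almost at p = 0.5, where p(1 − p) reaches its maximum of 25%.

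Under the same conditions a valid between-arm test falsely favours the intervention arm in 2.5% of trials if two-sided, and in 5% if one-sided.

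**3. Outcome list against schedule.**

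| Outcome | Outcomes {12} and instrument sections | Analysis section {20a} |
|---|---|---|
| Stress (IES-R) | t0, t1 | t0, t1 and t2 |
| Knowledge | t0, t1; change at t1 is secondary | not named |
| DCS at t2 | secondary | not named |

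Stress here cannot mean the HADS, because anxiety and depressive symptoms stand beside it in the same list.

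**The case against.** The primary question is already answered between arms. The independent t-test comes first, the paired test is only an addition, the sample size is built on the between-arm test, and nowhere is a within-arm p-value made a criterion for benefit. All of this stands. A reader might infer that the trial's main conclusion rests on within-arm change; the protocol does not support that.

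A reader might also infer that the repeated secondary outcomes will be tested within arms only. That is one reading of loose wording. The phrase may equally mean whichever test applies, mirroring the primary outcome. Additional analyses {20b} treats group allocation as an independent variable, and the objectives compare regret between the groups. What stands is the ambiguity.

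On size, one could quote the chance that exactly one arm is significant, 2p(1 − p), which is 34%, 50% and 28% at the first three dz values. That counts both directions. The misleading pattern that favours the aid is half of it. The dz values are also not from the protocol, and eligibility includes women recruited well after counselling, so the size of any natural fall is unknown.

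Finally, unadjusted between-arm tests of change are valid under randomisation, so baseline adjustment is a preference and not a correction. The stress visit and the omitted outcomes are small: the IES-R is not collected at t2, so that analysis could not be run.

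**Conclusion.** The point holds in a limited form. The plan adds within-arm significance tests that cannot address its hypothesis, does not call them descriptive, and words the repeated secondary outcomes so that a between-arm comparison is not assured.

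With 139 per arm, an ineffective aid and equal change in both arms, significance in the intervention arm only would arise in about 14% to 25% of trials for dz between 0.10 and 0.25. At dz 0.40 that pattern nearly vanishes, but both arms are significant about 99% of the time, so an ineffective aid would almost always show a significant fall. These figures are conditional on the assumed dz and on two-sided tests. They describe what would happen if within-arm results were read as evidence of efficacy, which the protocol does not say will be done.

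This should be corrected, but it does not threaten the primary comparison. The mismatch between the outcome list and the schedule is a minor reconciliation.

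**What to change.** Revise the paragraph in {20a}:

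1. Report within-arm change as mean with confidence interval, labelled as description, and remove the dependent t-tests as inference.
2. State that inference for each secondary outcome with a baseline (HADS anxiety, HADS depression, IES-R, knowledge, and DCS at t2) rests on the between-arm difference, preferably adjusted for the baseline value. Keep regret as a between-arm comparison at t2.
3. Compare the four-category SDM-S between arms with an ordinal or rank method.
4. Reconcile the outcome list with Outcomes {12} and the instrument sections: stress at t0 and t1 only, with knowledge at t1 and DCS at t2 added.

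The cost is small. All the data are already collected, the number of significance tests per outcome falls, and 139 (155 with dropout) per group is unchanged. Items 1 and 4 are wording. Baseline adjustment and an ordinal model, where adopted, are modest changes of method; a rank test is already within what the plan allows for non-normal data.

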#### Stage of decision-making

The stage of decision-making is measured using the Stage of Decision Making Scale (SDM-S) [52]. It consists of a single item with four or six response categories. In this study, an adapted German version with a four-answer category is used [61]. The categories used are (1) ‘I have not yet thought about the options’, (2) ‘I am considering the options’, (3) ‘I am close to choosing one option’ and (4) ‘I have already made a choice’. The SDM-S is administered at t0, t1 and t2.

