### Additional analyses {20b}

Subgroup analyses are planned to investigate whether there are differences in primary and secondary outcomes (1) between *BRCA1/2* mutation carriers without a personal history of cancer and those with a personal history of unilateral BC and (2) between women recruited directly after the post-test genetic counselling or later on at an appointment as part of an examination for the intensified breast cancer screening (and aftercare) programme. Subgroup analyses will be performed using the independent *t-*test for normally distributed metric variables, and non-parametric tests will be used in case of non-normal distributions. The chi-square test or Fisher’s exact test will be used for categorical variables. Beyond group allocation, demographic data will be used as the independent variable.

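### The four-category stage-of-decision item (SDM-S) is set up as an unadjusted mean change in codes; an ordinal model adjusted for t0 stage would be easier to interpret and more powerful

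*Protocol article*

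**What the plan says.** The section Stage of decision-making describes the SDM-S: "It consists of a single item with four or six response categories", and "an adapted German version with a four-answer category is used". The categories run from not having thought about the options to having chosen. The item is given at t0, t1 and t2.

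Outcomes {12}, in the text below Table 1, makes the t1 endpoint a change: "Secondary outcome variables at t1 include changes in SDM-S, HADS, IES-R and knowledge". For t2 the same text names SDM-S without the word change.

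Analysing primary and secondary outcomes {20a} then counts among the secondary outcomes the "mean differences in scores of the stage of decision-making" across the three time points, in one list with the stress and HADS scores. These are tested by dependent or independent t-test if normally distributed. The fallback is worded for the primary outcome as "Non-parametric tests will be used in case of non-normal distribution" and repeated for the secondary outcomes. Neither the non-parametric test nor the quantity it would rank is named, and baseline stage is not a covariate. The section also plans frequencies and percentages for categorical data.

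A test for categorical variables appears only under Additional analyses {20b}, for subgroups: chi-square, or Fisher's "exact test will be used for categorical variables".

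**The concern.** Two separate faults meet in this one outcome.

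- **Interpretation.** A mean of code differences gives every one-step move the same weight. Moving from not having thought about the options to considering them counts as much as moving from nearly decided to decided. A woman already at stage 4 at t0 can only stay or fall. A result such as a mean difference of 0.2 stages does not tell a clinician how many more women moved on.
- **Efficiency.** An unadjusted change score carries the noise of two measurements. Unless t0 and t1 stage are strongly correlated, it estimates the group effect less precisely than an analysis of t1 stage adjusted for t0 stage.

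The normality rule does not resolve this. A four-category item, or a difference of two such items with seven possible values from -3 to 3, cannot be normal. Read literally, the rule always leads to the unnamed test.

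At stake is how clear and how sensitive one secondary outcome is.

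**Working it through.** **1. The plan's own figure.** Sample size {14} concerns the primary outcome: d = 0.3, one-sided 0.05, power 0.8.

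- n per group = 2 × (1.645 + 0.842)² / 0.3² = 137.4, so 138. The exact t-test gives 138.07, so 139, as printed.
- 139 / 0.9 = 154.4, so 155 per group and 310 in total, as printed.

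There is no such figure for SDM-S. Only the 139 per arm is carried forward.

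**2. Why an unadjusted change score costs power.** With equal variances at t0 and t1 and correlation r, the variance of the group contrast is proportional to:

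- change score: 2(1 − r)
- t1 value alone: 1
- t1 adjusted for t0: 1 − r²

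Change against adjusted is 2(1 − r)/(1 − r²) = 2/(1 + r). At r = 0.24 this is 1.61; at r = 0.70 it is 1.18. So the loss is largest at low correlation. The t1 value alone against adjusted is 1/(1 − r²), which is 1.06 at r = 0.24 and 1.96 at r = 0.70, so that loss grows with correlation.

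**3. Simulation on the four-category scale.** All inputs except the 139 per arm and the 0.05 level are assumptions:

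- Marginal odds ratio 1.75. On the logistic scale that is ln(1.75)/1.814 = 0.31 SD, close to the d = 0.3 planned for the primary outcome.
- Two-sided 0.05. The protocol gives 0.05 without a side for secondary outcomes.
- Latent t0-t1 correlation 0.3 to 0.85, which gives a correlation of the codes of 0.24 to 0.70.
- Set 1: shares in stages 1 to 4 of 15/55/20/10% at t0, and 5/40/25/30% in controls at t1.
- Set 2: 10/40/25/25% at t0, and 5/25/25/45% in controls at t1.

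The odds ratio moves stage 4 at t1 from 30% to 42.9% in set 1 (0.30/0.70 × 1.75 = 0.75; 0.75/1.75 = 0.429). In set 2 it moves from 45% to 58.9% (0.45/0.55 × 1.75 = 1.432; 1.432/2.432 = 0.589).

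Power in %, 800 trials per row (Monte Carlo SE at most √(0.25/800) = 1.8 points):

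| Set, latent correlation | t-test on change | Mann-Whitney on change | Mann-Whitney on t1 stage | ANCOVA on codes | Ordinal model, t0 stage as factor |
|---|---|---|---|---|---|
| 1, 0.30 | 57.1 | 57.4 | 70.5 | 72.4 | 73.6 |
| 1, 0.50 | 69.0 | 67.9 | 70.2 | 77.9 | 79.5 |
| 1, 0.70 | 82.6 | 80.2 | 71.6 | 87.4 | 88.2 |
| 1, 0.85 | 90.6 | 89.9 | 71.9 | 93.2 | 94.2 |
| 2, 0.30 | 46.1 | 45.0 | 70.4 | 71.0 | 72.0 |
| 2, 0.50 | 57.8 | 55.0 | 70.2 | 75.4 | 76.4 |
| 2, 0.70 | 70.9 | 66.0 | 69.5 | 82.1 | 84.4 |
| 2, 0.85 | 82.2 | 79.0 | 67.8 | 90.9 | 93.9 |

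**4. Gaps to the ordinal model.**

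- t-test on change: from 94.2 − 90.6 = 3.6 to 72.0 − 46.1 = 25.9 points. A repeat with 300 trials per scenario gave about 3 to 20, so about 3 to 26 overall.
- Mann-Whitney on change: from 94.2 − 89.9 = 4.3 to 72.0 − 45.0 = 27.0 points. Ranking the change does not help.
- Mann-Whitney on t1 stage: from 72.0 − 70.4 = 1.6 to 93.9 − 67.8 = 26.1 points. A repeat with 2,000 trials gave this test 72 to 73% in set 1, which puts the smallest gap at about 1 point.
- ANCOVA on the codes: from 88.2 − 87.4 = 0.8 to 93.9 − 90.9 = 3.0 points. Treating the codes as numbers therefore costs little power once baseline is in the model.

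**5. No effect.** In 1,500 trials (set 1, correlation 0.5) the t-test on change rejected in 4.9% and the ordinal model in 5.4%. The false-positive rate is not the issue.

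**The case against.** The strongest reply is that the plan is looser than a quick reading suggests.

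- A reader might infer that SDM-S will simply be t-tested. The text does not say that: the t-test is conditional on normality, and the rule leads to a non-parametric test. This stands.
- That test is unnamed, and Outcomes {12} lists SDM-S at t2 without the word change. A rank test on stage itself would respect the ordering and equate no steps. This stands as a possible reading. At t1, however, the endpoint is explicitly a change, and {20a} describes mean differences between time points. Even on the generous reading the loss is small only at low correlation.
- A reader might infer that numeric coding of the categories is what costs power. ANCOVA on the same codes shows otherwise; the coding harms interpretation.
- Covariates are commonly left to an analysis plan, and none is shown. Silence on adjustment alone would be no finding. What the article does fix is the change-score form and its mean as the summary.
- A reader might infer that the trial will not show how many women reached a choice. Frequencies and percentages are planned for categorical data, so this is at least covered descriptively. Nor do the Objectives {7} name reaching a choice as an aim.
- The ceiling may be modest, since eligibility requires an open decision on at least one measure. A woman may still mark stage 4 for a decision already taken, so it need not be empty.
- The simulated data satisfy proportional odds marginally, which favours the ordinal model. The near-equality with ANCOVA shows that most of the gain comes from adjustment.

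**Conclusion.** The point holds as a modest improvement to a secondary outcome. The article states an analysis that fits a four-category ordinal item poorly: a mean change in codes, not adjusted for baseline, with the test chosen by a normality check that the item cannot pass.

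Under the assumptions shown, the t-test on change loses about 3 to 26 points of power against an ordinal model adjusted for t0 stage. An unadjusted rank test on t1 stage loses from about 1 point at low correlation to more than 20 at high correlation. The documents supply neither the stage distribution nor the t0-t1 correlation, so these are ranges and not forecasts.

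No reader should conclude that the result would be invalid, since type I error is near nominal. The primary analysis and the sample size of 310 are not touched either; SDM-S has no power calculation of its own.

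**What to change.** Take SDM-S off the mean-difference list in {20a}. Analyse stage at t1 and, separately, at t2 by proportional-odds regression on group, with t0 stage as a categorical covariate. Report the odds ratio with 95% CI, alongside the percentage at stage 4 by arm.

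The cost is a change of wording and a few lines of R, which the plan already names. No new data are needed, because SDM-S is collected at all three time points; closed recruitment is therefore no obstacle. The one added burden is that the proportional-odds assumption must be checked.
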